## Methods/design

### Objectives {7}

The primary aim of this trial is to determine the safety and tolerability of xanthohumol in healthy adults through administration of 24 mg/day of xanthohumol, compared to placebo. This aim will be met by assessing routine clinical toxicology measures compared to baseline values, including complete blood count, electrolytes, estimated glomerular filtration rate, blood urea nitrogen to creatinine ratio, aspartate aminotransferase (AST), alanine aminotransferase (ALT), ɣ-glutamyl transferase (GGT), alkaline phosphatase, and bilirubin, plus self-reported adverse events. The secondary aim is to measure effects of xanthohumol on TNF-α as a biomarker of active inflammation [14, 16, 24, 25]. The tertiary aim is to collect preliminary data related to effects on gut permeability, xanthohumol metabolism, and impact on the gut microbiome for a subsequent phase II trial in adults with Crohn’s disease based on mechanisms described in Table 1. Tertiary outcome measures include xanthohumol metabolites in the blood and urine; biomarkers of gut permeability, enterocyte inflammation, and systemic immune activity; assessment of bile acid metabolism; gut microbial composition; and identification of gut microbial proteins targeted by xanthohumol. Specific biomarker information by aim can be found in Table 2. Summary safety data will be reported upon trial completion as the frequency of new-onset laboratory abnormalities, including changes in anemia status, liver function tests (AST, ALT, GGT, bilirubin, and alkaline phosphatase), electrolytes, and/or creatinine and estimated glomerular filtration rate (eGFR).

**Table 2 Tab2:** Aims and methods of assessment

Aim	Marker	Assessment method
1. *Safety & Tolerability*	a. RBC, WBC, platelets b. eGFR, electrolytes, BUN:Cr, AST, ALT, GGT, alkaline phosphatase, bilirubin c. Adverse events, quality of life	a. Complete Blood Count (CBC) b. Comprehensive Metabolic Panel (CMP) c. Adverse Events Questionnaire, PROMIS-29
2. *Inflammation*	a. Inflammatory cytokines: IL-1β, IL-2, IL-6, IL-8, IL-10, TNF-α, and IL-12p70 b. Fecal calprotectin	a. Serum or plasma analysis b. Stool analysis
3a. *Gut Permeability*	a. CD14, lipopolysaccharide binding protein, intestinal fatty acid binding protein	a. Plasma analysis
3b. *Xanthohumol Metabolism*	a. Xanthohumol metabolite profiles	a. 24-hour urinalysis, plasma analysis, stool analysis

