### Laboratory analysis outcomes {12}, statistical methods {20a, 20b, 20c}

Relevant laboratory-based safety measures were chosen as the primary safety outcomes, because this trial is intended to precede a clinical trial in adults with Crohn’s disease—a clinical population potentially vulnerable to anemia, liver toxicity, renal abnormalities, etc. Therefore, a formal assessment of laboratory changes in healthy humans provides critical information to guide expectations for changes in laboratory markers and associated adverse clinical effects in future research in Crohn’s and other clinical populations.

The primary objective’s laboratory-based outcome domains (and corresponding measures) are liver function (AST, ALT, alkaline phosphatase, bilirubin), renal function (BUN, creatinine, estimated glomerular filtration rate), hematology (red blood cell count, hematocrit, hemoglobin, white blood cell count), and electrolytes (sodium, potassium, calcium, chloride) measured every 2 weeks for 8 weeks. The primary outcome metric for comparison between study groups is the mean change from baseline to week 8. However, all parameters will be similarly evaluated at each follow-up time point, by formally comparing mean change from baseline to follow-up between groups. Comparisons at a single follow-up will use 2-sided independent *t* tests; omnibus tests for differing trends over time will employ linear mixed models with time point as a repeated factor and study group as an independent factor.

Primary outcome laboratory measures will be analyzed by first assessing descriptive statistics including mean, median, and standard deviation. All distributions will be tested for skew and transformed (e.g., natural log transformed) as needed to reduce the influence of skew in subsequent analyses. If inspection of distributions indicates significant non-normality that cannot be corrected with standard transformations, significance will instead be calculated using a non-parametric Wilcoxon signed rank test. The primary analysis will be a per-protocol analysis as this trial is a phase I trial focused on clinical toxicity, not a definitive efficacy or effectiveness trial; therefore, we are investigating the clinical and mechanistic effects of the product for those participants who took the experimental agent only. As a sensitivity analysis, missing laboratory data will be imputed by multiple imputation to assess the robustness of study results to imputation.

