As an element of the evaluation for safety of the intervention, the percentage of laboratory newly abnormal (for values that were within the clinically normal range at baseline) per clinical laboratory reference ranges for each lab parameter will be reported at each time point and the percentage will be compared between groups by Fisher’s exact test. Assessment for changes in the distribution of each lab parameter will be performed by presenting means and confidence intervals (CI) for the change in each group, as well as the mean CI for the difference between groups; significance will be tested using 2-sided, unpaired *t* tests (or, if inspection of distributions indicates strong non-normality, with a non-parametric Wilcoxon signed rank test) of the mean values for the xanthohumol group compared to the placebo group. Assessment for overall *increases* or *decreases* in collected parameters will be tested for linear trends of the means by linear mixed ANOVA, considered significant if *p* < 0.05, with time point as a repeated factor. This may be suggestive of evidence for cumulative toxicity if trending in a clinically deleterious direction.

Health-related quality of life, measured by PROMIS-29, is included as a tertiary measure of gross changes in health. PROMIS-29 includes 7 validated subscales (physical function, anxiety, depression, pain intensity, pain interference, sleep, social interactions), each of which will be calculated as a mean by group, and means will be compared between xanthohumol and placebo, with the primary comparison being of mean changes from baseline to week 8. Significance of changes in QOL measures will be tested according to the same plan outlined for laboratory markers, above.

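### The between-group frequency of laboratory abnormalities counts only values that were normal at baseline, so worsening from an already abnormal baseline is left out of it

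*Protocol article*

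**What the plan says.** The section on laboratory outcomes and statistical methods describes a per-parameter, per-time-point outcome: "the percentage of laboratory newly abnormal (for values that were within the clinically normal range at baseline) per clinical laboratory reference ranges". The restriction at issue is the part in brackets, "for values that were within the clinically normal range at baseline". The section adds that "the percentage will be compared between groups by Fisher’s exact test". The sentence opens by giving this outcome its place: "As an element of the evaluation for safety of the intervention". Objectives {7} uses the same idea for the end-of-trial safety summary, which is to be reported as "the frequency of new-onset laboratory abnormalities, including changes in anemia status, liver function tests (AST, ALT, GGT, bilirubin, and alkaline phosphatase", together with electrolytes and renal measures.

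The main laboratory comparison is a different one: "The primary outcome metric for comparison between study groups is the mean change from baseline to week 8". It is repeated over time: "all parameters will be similarly evaluated at each follow-up time point, by formally comparing mean change from baseline to follow-up between groups". Neither statement is limited to participants with normal baseline values. The same holds for the linear trend analysis, and for the laboratory withdrawal and suspension rules under Criteria for discontinuing {11b, 21b}.

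The reason given for choosing laboratory safety measures is the planned later trial in Crohn's disease, "a clinical population potentially vulnerable to anemia, liver toxicity, renal abnormalities, etc".

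**The concern.** A participant just outside the limit for ALT at baseline whose value then rises several-fold, or one with mild anaemia whose haemoglobin falls further, gives no newly abnormal value for that measure and is not in its denominator. The eligibility table, as printed, lists no laboratory limit, and excluding a history of chronic disease does not exclude an unnoticed out-of-range result.

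The frequency of abnormalities matters in this plan. The Hypotheses section frames safety as the frequency of laboratory abnormalities or adverse events, and Sample size {14} powers the trial on the proportion with either. The only analysis definition of a laboratory abnormality in the article is the one limited to normal baselines. What is at stake is whether a reader of the safety table would see the few participants who started abnormal and got worse. The question would matter more in a patient trial that took over the same definition.

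**Working it through.** **The plan's own figures.** The article gives no number for this restriction. Its sample size does not depend on the point. With 12 per group, the normal approximation gives power 0.802 at 5% versus 55%, so the stated 80% is reproduced at that assumed control rate. The enrolment figure follows from 12 / (1 − 0.25) = 16 per arm, or 32 in all.

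**Inputs.**
- Participants: 12 evaluable per arm, 32 at full enrolment (Sample size {14}).
- Measures: the statistical methods section lists 4 liver, 3 renal, 4 haematology and 4 electrolyte measures, 15 in total.
- Proportion of baseline values outside the reference range: not given. I assume 2.5% to 5%, where 5% corresponds to limits that cover the central 95% of healthy people.

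**Participants left out of one parameter's Fisher comparison, per arm of 12.**
- 12 × 0.025 = 0.3
- 12 × 0.05 = 0.6
- Chance that at least one of 12 is left out: 1 − 0.975^12 = 0.26 and 1 − 0.95^12 = 0.46

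**Participant-parameter pairs left out at full enrolment.**
- 32 × 15 = 480 pairs
- 480 × 0.025 = 12
- 480 × 0.05 = 24

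The 12 to 24 are expected counts and need no independence between measures. They count everyone out of range at baseline. Those who then also worsen are fewer, and the article gives no basis for estimating that number.

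**Does mean change show the same event?** Suppose k of n participants in one arm have the same very large rise and all other changes are negligible. The two-sample t statistic then tends to √[k(n − 1)/(n − k)], whatever the size of the rise.

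| k of 12 versus 0 of 12 | t (22 df) | t-test p | Fisher p |
|---|---|---|---|
| 1 | 1.00 | 0.33 | 1.0 |
| 2 | √(22/10) = 1.48 | 0.15 | 2 × 66/276 = 0.48 |
| 3 | √(33/9) = 1.91 | 0.07 | 2 × 220/2024 = 0.22 |

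With one such participant in 16 per arm, t is again 1 and p = 0.33. Transforming for skew or using a rank test, both of which the plan allows, would reduce the influence of such values further.

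Fisher's test does not detect one to three events either. The gain from counting is therefore not power. A count or shift table displays the individual worsening, and a group mean does not.

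**The case against.** The strongest reply is that the definition is deliberate and coherent. A new-onset outcome limited to those who can have a new onset is a standard measure, Objectives {7} and the statistical section agree on it, and the plan calls it one element of the safety evaluation. The population is healthy adults, so few values are affected. Shift tables and worsening grades are often left to an analysis plan, which is not shown here. Most of this stands, and it keeps the point small. It does not remove the point, because the article itself fixes the restriction and states no other definition of a laboratory abnormality for analysis.

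Three stronger readings are tempting, and the document does not support them.

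- **Worsening from an abnormal baseline never counts as toxicity.** It does count elsewhere: in the primary mean change, in the mixed models and in the trend analysis, which the plan links to cumulative toxicity. A critical value leads to withdrawal, and persistent abnormalities count toward suspension, in both cases without requiring a normal baseline. What remains true is that means dilute one or two cases, and that the withdrawal and suspension rules govern conduct and are not a reported comparison between arms.
- **The rule biases the result towards safe.** The restriction depends on a baseline value and applies equally to both masked, randomised arms. Those left out leave the numerator and the denominator together. The rate would be understated only if baseline-abnormal participants worsen more often than others become abnormal, and the article gives no evidence on that.
- **About half of participants are affected.** One can compute 1 − 0.95^15 = 0.54, but this assumes 15 independent measures. Red cell count, haematocrit and haemoglobin move together, as do creatinine and eGFR, so the figure is probably too high. It also matches no planned analysis, because the percentage is compared parameter by parameter.

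**Conclusion.** The point holds in a limited form. Worsening from an abnormal baseline is missing from the one between-group frequency comparison of laboratory abnormalities that the plan defines. On the assumed 2.5% to 5% out-of-range rate, that is less than one participant per arm of 12 for any single parameter. The rate counts both tails, including directions that are not adverse, so the relevant number is smaller still. It also rests on the eligibility table as printed, and the full protocol may contain a laboratory entry limit. Neither a bias between arms nor a gap in participant protection is shown. This is a cheap improvement to the safety display and not a flaw that threatens the trial's conclusion.

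**What to change.** Keep the new-onset percentage as it is. For each parameter, add a treatment-emergent category: either a new abnormality from a normal baseline, or worsening from an abnormal baseline in the adverse direction by a threshold fixed before unmasking. The clinical investigators should choose that threshold, and none is proposed here. Use all participants with a baseline and a follow-up value as the denominator, and compare the arms by Fisher's exact test. Add a baseline-to-worst shift table by arm.

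The data are already collected every 2 weeks. The cost is about one sentence of definition, one extra table, and agreeing the threshold in advance.

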### Criteria for discontinuing or modifying allocated interventions {11b, 21b}

A participant may be withdrawn from the trial at any time they choose, due to adverse events or at their request. However, participants will be actively withdrawn if they demonstrate any new onset, moderate, or more severe adverse events attributable to the intervention. Participants will also be withdrawn if they have any critical value return on routine clinical laboratory measures of safety, including significant changes in blood cell counts, liver function tests, or renal function tests. The trial will be suspended if > 20% of study participants experience moderate or greater severity adverse events or laboratory abnormalities contributing to halting criteria including abnormal calcium, sodium, potassium, creatinine, or GFR; anemia; and/or abnormal elevations in bilirubin, elevated alkaline phosphatase, AST, or ALT that are persistent upon repeat testing.

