### Sample size {14}

A sample size of twenty-four (*n* = 12 per group) provides 80% power to detect a 50% difference in proportions of participants between groups by chi-squared test experiencing a laboratory abnormality or adverse event at a significance threshold of *α* = 0.05. To account for up to 25% attrition, up to 16 adults (8 biologically male and 8 biologically female participants) will be enrolled in each study arm. Given that this phase I trial is intended as a step toward a phase II clinical trial in Crohn’s disease, for which few effective treatments exist, the investigational drug is commonly available in the diet, and previous human studies have not suggested any toxicity, the present trial was powered to detect gross toxicity resulting in frequent adverse events and/or laboratory-measurable toxicity. However, interim halting criteria were also used to assess safety; an accumulated frequency of 25% reaching laboratory halting criteria was pre-specified as a criterion for halting the trial and requiring detailed review by the FDA, NCCIH, and IRB.

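### The laboratory event states no harmful direction or size, so a trivial crossing counts like a marked rise, and the participant-level frequency behind the hypothesis and the power statement would be high with no drug effect

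*Protocol article*

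**What the plan says.** Under *Laboratory analysis outcomes {12}, statistical methods {20a, 20b, 20c}*, the event is a newly abnormal result ("for values that were within the clinically normal range at baseline"). Its percentage "per clinical laboratory reference ranges for each lab parameter will be reported at each time point". No direction, grade or multiple of a limit is given. On testing, the section says that "the percentage will be compared between groups by Fisher’s exact test". It also sets the main laboratory metric: "The primary outcome metric for comparison between study groups is the mean change from baseline to week 8".

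Two other sections use a frequency per participant. *Hypotheses* judges safety by how often laboratory abnormalities or adverse events occur in each arm. *Sample size {14}* says that the planned total of 24 "provides 80% power to detect a 50% difference in proportions of participants between groups by chi-squared test experiencing a laboratory abnormality or adverse event". Neither section defines a laboratory abnormality further.

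Direction and persistence do appear in the halting criteria, under *Criteria for discontinuing or modifying allocated interventions {11b, 21b}*, where the liver items are "abnormal elevations in bilirubin, elevated alkaline phosphatase, AST, or ALT that are persistent upon repeat testing".

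**The concern.** The primary aim is to learn whether the product causes laboratory toxicity. The event rule does not distinguish a result just past a limit from one several times the limit. As written, it also does not distinguish a low AST from a high one.

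For one analyte at one visit this is a loss of information. For the participant-level frequency it matters more. With many analytes and repeated visits, most healthy untreated people may have some new out-of-range value. A proportion that is already high in the placebo arm cannot rise by the amount the trial was sized to detect, and a similar frequency in both arms would then say little about safety.

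**Working it through.** **Inputs from the article**
- Analytes: "liver function (AST, ALT, alkaline phosphatase, bilirubin), renal function (BUN, creatinine, estimated glomerular filtration rate") gives 4 + 3; hematology adds 4; "electrolytes (sodium, potassium, calcium, chloride) measured every 2 weeks for 8 weeks" adds 4. Total 15.
- Follow-up visits: 8 / 2 = 4.
- Sizing: 12 per arm, 80% power, α = 0.05 (taken as two-sided), 50% difference, control rate not stated.

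**Assumptions (the article gives no background rate)**
- Each reference range covers the central 95% of healthy people (±1.96 SD, Gaussian).
- The between-person share of variance, r, is 0.5 to 0.85.
- Only values normal at baseline can count, as the plan says, and crossings in both directions count, because none is excluded.

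**1. The plan's own figure**

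n = [1.96·√(2·p̄·(1−p̄)) + 0.8416·√(p₁(1−p₁) + p₂(1−p₂))]² / (p₂−p₁)².

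For 5% vs 55%: (1.96·√0.42 + 0.8416·√0.295)² / 0.25 = (1.270 + 0.457)² / 0.25 = 11.9, so 12.

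| Control vs xanthohumol | n per arm | Power at n = 12 |
|---|---|---|
| 0% vs 50% | 11 | 86% |
| 5% vs 55% | 12 | 80% |
| 10% vs 60% | 14 | 76% |
| 25% vs 75% | 15 | 71% |
| 45% vs 95% | 12 | 80% |

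So 12 per arm reproduces near a 0–5% control rate, or in the mirror case where 95–100% of the xanthohumol arm has an event. The 50% must be percentage points. Read as relative, control rates of 20%, 40% and 60% would need 294, 97 and 32 per arm.

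**2. One analyte, one visit (the unit of the planned Fisher tests)**

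P(new | normal at baseline) = 1 − P(both within limits) / 0.95.
- r = 0.5: 1 − 0.9093 / 0.95 = 4.3%.
- r = 0.85: 1 − 0.9254 / 0.95 = 2.6%.

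**3. Any laboratory event per participant over 4 visits**

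Simulation gives the chance of at least one new crossing in one analyte over four visits. With k independent analytes, P(any) = 1 − (1 − that chance)^k. Repeat runs differ by about one percentage point.

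| r | One analyte, 4 visits | k = 15 | k = 8 |
|---|---|---|---|
| 0.5 | 13.3% | 88% | 68% |
| 0.7 | 9.9% | 79% | 57% |
| 0.85 | 6.6% | 64% | 42% |

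The k = 8 column allows for overlap between analytes such as red cell count, hematocrit and hemoglobin. A pairwise correlation of 0.3 among all 15 gives 83% at r = 0.5 and 73% at r = 0.7. Adverse events, collected with an 81-item questionnaire, can only raise the composite.

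**4. Effect on the power statement**

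At a 65–80% control rate the largest possible increase is 100 − 65 = 35 down to 100 − 80 = 20 points. Even if every xanthohumol participant had an event, chi-squared power with 12 per arm would be 65% (control 65%), 51% (70%) and 21% (80%). With all 16 retained it would be 87%, 75% and 40%.

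**5. What lowers the background**
- One direction for 10 analytes, with the four electrolytes and WBC two-sided: about 49–75% still have an event.
- One direction for all 15, with a limit at 3 SD: about 4–7% (r = 0.8 to 0.5).

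Magnitude does most of the work; direction alone does not.

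**6. Masking within one analyte**

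Five marked rises against none: Fisher p = 2·C(12,5)/C(24,5) = 2·792/42504 = 0.037. With one trivial crossing in the placebo arm, 5/12 vs 1/12 gives p = 2·(792·12 + 924)/134596 = 0.155. The chance of at least one such crossing among 12 placebo participants at one visit is 1 − 0.974¹² = 27% to 1 − 0.957¹² = 41%.

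**The case against.** The best defence is that the section compares each analyte at each time point separately. There the untreated rate is a few percent, ALT is compared only with ALT, and reporting new out-of-range percentages is conventional. This stands. A reader might infer that most untreated participants would trip those tests; they would not. The high figures apply only to the participant-level frequency.

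A reader might also infer that no laboratory analysis carries size, so that a toxic rise would vanish. The article does not support this. Mean change to week 8 is the main laboratory metric, and it carries size and sign. Participants with critical values are withdrawn, halting criteria use laboratory results, the monitoring board reviews abnormal values, and the Discussion describes a composite safety assessment with regulatory input. What remains is narrower. Mean change dilutes one person's rise: one of 12 going from an ALT of about 20 to 200 U/L gives a median p of 0.33 in simulation. A withdrawn participant may also have no week 8 value.

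That example cannot be pressed further. One case against none gives Fisher p = 1.0 under the plan and under graded categories alike. It shows the limit of 12 per arm, and the article says openly that it is powered for gross toxicity.

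Finally, grading and shift tables are often left to an analysis plan, and that both directions count is read from silence. Both are fair. The point is not that tables are missing. The article fixes an event rule, and its hypothesis and sample size depend on a frequency that has only that rule behind it.

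**Conclusion.** The point holds as a cheap improvement to the analysis, not as an error in the per-analyte comparisons. Within an analyte, the stated event does not separate a trivial crossing from a marked change. Carried to the participant level, as *Hypotheses* and *Sample size {14}* require, it would give about 64–88% of untreated participants at least one laboratory event over four visits, or 42–68% with 8 effective analytes. Above 50% the planned 50-point increase cannot occur. Near the low end it is possible only if almost all xanthohumol participants have an event.

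These percentages rest on assumed 95% reference ranges, Gaussian values, r between 0.5 and 0.85 and, for the first range, independent analytes. Higher r lowers them: 54% at r = 0.9 with 15 analytes.

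**What to change.** In the statistical methods section:
- For each analyte, state the harmful direction (or both), and take each participant's worst post-baseline value in that direction.
- Grade it by magnitude, using a named version of the terminology criteria on which the adverse event questionnaire is already based. The grade definitions printed under *Adverse event reporting and harms {22}* are worded around daily activities and treatment, so they cannot grade a laboratory value. State the lowest grade that counts as an event; it needs to lie clear of the reference limit if the background is to fall.
- Show worst-grade shift tables by arm with an exact comparison, and list every marked change individually, including values from withdrawn participants.
- Keep the any-out-of-range percentages as descriptive.

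In *Hypotheses* and *Sample size {14}*, say that the laboratory part of the frequency is this graded event, and give the control rate assumed. Reconcile the event's direction and persistence with the wording of the halting criteria; which clinical rule should apply is for the investigators.

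The cost is wording and a few added tables; no new data are needed. Graded events are rarer, so reported percentages will be lower. A single case will still not reach significance, but severity becomes visible and a cluster of marked changes is not masked by trivial ones.

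### New laboratory abnormalities are tested only visit by visit for each parameter; no stated test counts a participant once over the 8 weeks, so abnormalities that resolve or end in withdrawal can be missed

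*Protocol article*

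**What the plan says.** The section on laboratory outcomes and statistical methods defines the quantity as "the percentage of laboratory newly abnormal (for values that were within the clinically normal range at baseline) per clinical laboratory reference ranges". It then says that this percentage "will be reported at each time point and the percentage will be compared between groups by" Fisher's exact test, parameter by parameter. New is judged against baseline only. The laboratory measures are "measured every 2 weeks for 8 weeks", which gives four follow-up visits and four tables per parameter.

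Three other sections describe the question over the whole trial:

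- Objectives {7}: "Summary safety data will be reported upon trial completion as the frequency of new-onset laboratory abnormalities". It gives neither a unit of counting nor a test.
- Hypotheses: safety is judged by how often laboratory abnormalities or adverse events occur in one group against the other.
- Sample size {14}: 12 per group are said to give "80% power to detect a 50% difference in proportions of participants between groups", where the participant counts as affected on a laboratory abnormality or an adverse event, compared by chi-squared test.

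The section on discontinuing the intervention adds: "Participants will also be withdrawn if they have any critical value return on routine clinical laboratory measures of safety". It also withdraws participants for new moderate or worse adverse events attributable to the intervention.

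**The concern.** A percentage abnormal at a visit and the proportion of participants ever newly abnormal are different quantities. Someone abnormal at week 2 and normal afterwards is a case in the week-2 table and a non-case in the next three. Someone withdrawn for a critical value at week 2 would have no later scheduled samples, and so would presumably leave the later tables (the article does not state the denominators). Toxicity with scattered onset is thus divided over four small tables, and nothing stated puts the pieces together even within one parameter such as ALT.

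At stake is the sensitivity of the one stated between-group test of new laboratory abnormalities, in a trial whose sample size rests on a proportion of participants.

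**Working it through.** **1. The plan's own figure.** The article gives 12 per group, 80% power, a 50% difference and α = 0.05, but no control rate. Read as 50 percentage points, with a two-sided pooled-variance formula and an assumed 5% vs 55%:

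n = [1.96·√(2·0.30·0.70) + 0.842·√(0.05·0.95 + 0.55·0.45)]² / 0.50² = (1.270 + 0.457)² / 0.25 ≈ 11.9, so 12 per group.

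Allowing for 25% attrition, 12 / 0.75 = 16 per arm. Both stated figures reproduce. At 0% vs 50% the formula gives 11, and at 10% vs 60% it gives 14. The planned quantity counts each participant once.

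**2. What one visit needs.** With 12 per arm and no placebo cases, the two-sided Fisher p for *a* cases is 2·C(12,a)/C(24,a):

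| Cases | p |
|---|---|
| 1/12 vs 0/12 | 1.00 |
| 2/12 vs 0/12 | 0.478 |
| 4/12 vs 0/12 | 0.093 |
| 5/12 vs 0/12 | 0.037 |
| 6/12 vs 0/12 | 0.014 |

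At least five participants must be abnormal at the same visit.

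**3. One worked case.** Take six xanthohumol participants newly abnormal on one parameter and none on placebo, with onsets 1, 2, 1, 2 over the four visits.

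- Counted once per participant: 6/12 vs 0/12, p = 0.014.
- Each abnormality lasting one visit: p = 1.00, 0.48, 1.00, 0.48.
- Each case withdrawn after its abnormal visit (1/12, 2/11, 1/9, 2/8 vs 0/12): p = 1.00, 0.22, 0.43, 0.15.

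**4. Range over duration.** Simulation, 20,000 trials per setting, 12 per arm, onset uniform over weeks 2, 4, 6 and 8. Rates, onset pattern and duration are assumptions; the article gives none of them.

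| Pattern | 50% vs 0%: any visit p<0.05 | 60% vs 10%: any visit p<0.05 |
|---|---|---|
| Lasts one visit | 5% | 7% |
| Lasts two visits | 37% | 39% |
| Lasts three visits | 66% | 58% |
| Persists to week 8 | 81% | 67% |
| Every case withdrawn after onset | 25% | 32% |
| **One participant-level test** | **81%** | **64%** |

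The 67% slightly exceeds 64% because it allows four chances of significance against one.

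The withdrawal row is the extreme of that mechanism. Withdrawal follows a critical value or an attributable moderate or worse event, not every value outside the reference range.

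**5. With 16 per arm** (full enrolment, no attrition), at 50% vs 0%: one visit about 16%, two visits about 71%, persistent 96%, all withdrawn 45%, against 96% for the participant-level test.

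**The case against.** The case on the other side is substantial.

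- **The loss depends on duration.** Under continued daily dosing, an abnormality may well persist. Then the week-8 table holds every case and nothing is lost. This stands. A reader might infer that no visit can ever reach significance, or that week 8 is always the least informative visit. The table above contradicts the first. The second fails for persistent or cumulative toxicity, which the same section sets out to look for.
- **This is one element among several.** The primary metric is mean change to week 8, with t tests at each visit and mixed models over time, and the Discussion describes a composite judgement of safety. This stands too: a reader might infer that the trial would declare the product safe on these Fisher tests, but no such decision rule is stated. Mean change nevertheless answers another question, since a few excursions that resolve can leave the week-8 mean unmoved.
- **Serious cases accumulate under the halting rules.** They do, but those rules act on all participants together and give no comparison between groups.
- **A participant-level comparison is already implied, and its details belong in a fuller document.** The sample size section does name such a comparison, but as a composite with adverse events and not for a laboratory parameter. The statistical methods section is not silent on the derivation: it fixes a test per visit. The handling of withdrawn participants in the denominators is inferred, not stated.
- **The 50% target is not a per-parameter target.** Correct. The 50% vs 0% above is an illustration for one parameter. A reader might infer that the planned power is lost, but the planned endpoint is the composite, so the documents do not support that.

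**Conclusion.** The concern holds in a limited form. The only stated between-group test of new laboratory abnormalities is a point prevalence per parameter and visit, while three other sections frame the question over the trial or by participant. For abnormalities that resolve, or that end in withdrawal, this element can miss a large difference. At 50% vs 0% with 12 per arm, the chance of a significant visit is about 5% to 66% for durations of one to three visits, and 25% if every case were withdrawn, against 81% for one participant-level test. There is no loss when abnormalities persist. These sizes rest on the assumed rates, uniform onset and two-sided Fisher tests at 0.05. It is worth correcting, but it does not undermine the safety evaluation as a whole.

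**What to change.** In the section on laboratory outcomes and statistical methods:

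1. For each parameter, count a participant with a normal baseline value once if any post-baseline value through week 8 is abnormal.
2. Keep participants withdrawn early in the denominator, with their events up to withdrawal.
3. Compare groups once per parameter by Fisher's exact test, and keep the percentages at each visit as description.
4. To match the sample size section, also report the proportion of participants with any new laboratory abnormality or adverse event. The per-parameter count alone does not supply the quantity on which the trial was sized.

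The cost is wording only: no new data, and one test per parameter in place of four. The drawback is a higher background rate in both arms. For example, an assumed 5% chance of an out-of-range value per visit, independent between visits, becomes 1 − 0.95⁴ ≈ 19% over four visits. Power for a 50-point difference falls as background rises: exact Fisher power with 12 per arm is 81% at 0% vs 50%, 64% at 10% vs 60% and 61% at 25% vs 75%.
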